## Abstract

**Background:**

Among the most urgent public health challenges, of the twenty-first century, is obesity. This can be attributed to its relationship with several non-communicable diseases (NCDs), as well as premature mortality. Being overweight or obese is a major concern not only in high-income countries, but also in low-income and middle-income countries, particularly in urban areas. Several studies have highlighted the prevalence of obesity, among Middle Eastern-descent adolescents, studying in Arabic secondary schools, located in Malaysia. Intervention studies, directed at Middle Eastern adolescents in Malaysia, are limited. This paper, describes the protocol, for an integrated health education intervention process. Titled ‘Healthy lifestyle’, it is a primary prevention process, aimed at curbing obesity and disordered eating, among Middle Eastern secondary school adolescents, aged 13–14 years old, residing in Malaysia.

**Methods and anticipated results:**

A cluster randomized controlled study will be conducted, involving 250 Middle Eastern adolescents, in Arabic schools in Malaysia. The participants will be randomly assigned to the intervention and control groups. While the intervention group participates in six weeks of fortnightly six sessions (45 minutes per session), the control group will carry on with their regular curriculums, and normal physical activity routines. The variables which will be evaluated include anthropometric measurements, knowledge, attitude, daily routines, physical activity, sedentary behaviour, food assessment, eating attitudes test-26, and a structured questionnaire based on the HBM. Data will be collected from the intervention and control groups at baseline, post-intervention, and two months following the intervention. Data analysis will be performed by way of the SPSS Statistics software version 26. The generalized estimating equation (GEE) will be used, to test the effect of the intervention program, with regards to the selected variables (outcomes), between and within-group at baseline, as well as six weeks and two months following intervention, after adjusting for clustering. Outcomes will be assessed at each time point, along with a derived average over all three-time points; thus, ensuring that both the cumulative and overall effects are determined.

**Conclusions:**

This trial will provide useful information for improving the knowledge, attitude, and practices of Middle Eastern adolescents, with regards to body weight status, physical activity level, nutrition status (BMI and dietary intake), and disordered eating. This will go a long way, towards ensuring their adherence to appropriate physical activities, and a healthy diet, to keep non-communicable diseases at bay.

**Trial registration:**

This study is registered at NCT: NCT05694143.

## Introduction

One of the most urgent public health challenges of the twenty-first century is obesity. This is due to its association with several non-communicable diseases, as well as untimely mortality [1]. The World Health Organization (WHO) considers obesity and overweightness health risks, stemming from the presence of excess fat in the body. The assessment of obese and overweight persons by the WHO, involves the use of the body mass index (BMI) [2]. More than 1.3 billion people are obese because of globalization, urbanization, and an increasingly sedentary lifestyle, with the number anticipated to rise to 2 billion by 2030 [3]. Meanwhile, the WHO has declared, that the escalating epidemic of obesity, could significantly increase the risk of NCDs in many countries [4].

Adolescents, who the World Health Organization defines as those between 10 and 19 years old, are generally considered a healthy population [5]. Nevertheless, overweight, and obese adolescents, particularly in urban areas, are a growing concern, not only in high-income countries, but also in low-income and middle-income countries. The worldwide number of overweight and obese adolescents currently stands at approximately 60 million [6]. Sedentary behaviour, lack of physical activity, socioeconomic position, and a high intake of fat-rich foods, are among the factors leading to obesity and overweightness [7].

Urbanization brought about the change in adolescent dietary habits, from traditional foods to fast and convenient foods, culminating in the consumption of less amounts of fruits and vegetables [8]. According to the Centre for Disease Control (CDC), obesity prevalence among adolescents aged 12 to 19 years old, has increased from 5% in 1980, to over 21% in 2012 [9]. Additionally, according to the WHO, a more sedentary lifestyle, and less physical activity, has rendered 81% of school-going children, physically inactive [2].

Several surveys have confirmed that the prevalence and incidence of obesity, in the Middle East, will increase over the next few decades, suggesting that an unimpeded epidemic of obesity, will sweep across the region, soon. Consequently, the incidence of NCD has also risen in tandem, and represents more than 50% of the total cause of death, in the Eastern Mediterranean region (EMR) [10, 11]. In response to the growing level of obesity in children and adolescents throughout the EMR, the WHO proposed that action be taken, particularly as the issue of nutrition transition is evident in the area [1]. The prevalence, of overweight and obese Middle Eastern adolescents, is also on the rise. For example, in the case of Kuwait, it currently stands at 50.5% and 46.5% for adolescents aged 14 and 19 years old respectively. Another study in Iraq, involving secondary school students aged 13 to 17 years old, revealed the obvious prevalence of overweightness and obesity [9]. The issues leading up to obesity are considered complex and multifactorial.

In the Middle East, adolescents are inclined towards unhealthy dietary practices, and are generally lacking in knowledge regarding healthy and energy-dense foods [12]. Additionally, according to data deriving from eight countries in the EMR, the levels of physical inactivity range from about one-third, to as high as 70% of the population [13]. In Malaysia, Middle Eastern adolescents are experiencing changes in their living status, as they have increased access to energized food, enjoy a better transportation network (which reduces the need for physical movement activity), and frequently eat at western fast-food outlets. Thus far, investigations on the prevalence of overweightness and obesity, among Arabic secondary school students, are deemed very rare [9, 14]. The establishment and maintenance of a healthy diet, and a physically active lifestyle, call for intervention in the form of knowledge, attitude, and behavioural skill development. Of late, the number of intervention studies, focussing on the prevention and control of adolescent obesity, has been on the rise [15].

Schools are considered potential locations for a variety of fitness or multi-component programmes [16]. School-based interventions, in many regions, have delivered positive outcomes [15]. The findings, derived through several studies, indicate that changes in dietary behaviours, and physical activity, are key factors during efforts to reduce the occurrence of obesity among adolescents [17]. These efforts are deemed successful, when a weight loss of between 5% and 10%, is achieved by an individual [18]. The results from previous studies, suggest that certain theory-based educational programmes, which incorporate cognitive frameworks, can deliver a positive impact, on an individual’s behaviour [19]. The health belief model (HBM), an established model for many health education programmes, facilitates a better understanding of human attitudes, behaviours, and educational needs. This information is then utilized, for the development of effective interventions [20, 21].

Due to its reliability, we employed the HBM as the theoretical framework, for the development of a health education programme, during this randomized controlled trial. To the best of our knowledge, this represents the only educational programme, to apply intervention based on the HBM, to reduce the occurrence of obesity and overweightness among Middle Eastern adolescents, through alterations in their lifestyle and behaviour. This educational programme is designed, to promote the adherence to a positive lifestyle, among the target population, in terms of an appropriate diet, and favourable physical activity. This study delves into the effect of an HBM-based education programme, on the physical activity and eating behaviour, among Middle Eastern adolescents in Malaysia.

## Materials and methods

### Study design

The cluster randomized controlled trial (RCT), employed for this study, is considered a formidable technique, when it comes to the management of the subject’s characteristics, and threats to its internal validity [22]. A cluster randomized controlled trial design is frequently employed in health intervention research, as it compares individuals connected to specific institutions. Assessments are conducted at baseline, post-intervention, and during follow-up after two months, as shown in Fig 1 [23].

**Fig 1 pone.0289937.g001:**
[figure not shown]
SPIRIT schedule of enrolment, interventions, and assessments.

### Conceptual model

Health behaviour theories are theoretical frameworks that help explain and predict human behaviour related to health and disease. These theories identify the factors and determinants influencing health behaviour, such as eating habits, physical activity, substance abuse and other lifestyle choices. The most popular theories and applied models in the field of health behaviour include the Health Belief Model (HBM), the Social Cognitive Theory (SCT), the Trans-Theoretical Model (TTM) and the Theory of Planned Behaviour (TPB).

The Health Belief Model (HBM) assumes that individuals’ health behaviours are influenced by their perceptions of vulnerability to health risks, the severity of those risks, and the potential benefits of interventions to reduce those risks [20, 21, 24]. In the context of school-based obesity interventions, the HBM can be used to encourage students to take action to reduce their obesity risk by emphasising the negative consequences of unhealthy behaviours and the benefits of healthy behaviours. The HBM has some limitations, including not adequately addressing some of the individual factors that influence health behaviours. It also does not consider the influence of social variables on a person’s health choices [20, 21].

Social cognitive theory (SCT) assumes that social, environmental and personal factors influence behaviour. In the context of school-based obesity interventions, social cognitive theory can promote healthy behaviours by creating a supportive environment and emphasising the importance of self-efficacy and positive reinforcement [25]. The theory can be applied to develop appropriate interventions, such as exercise programmes for female students to combat obesity. In SCT, it is assumed that changes in the environment automatically produce changes in the person, although this is not always the case. The theory is loosely constructed and based solely on the dynamic interplay between person, behaviour and environment.

The Trans-Theoretical Model (TTM) assumes that behaviour change occurs in stages and that individuals progress through these stages as they become more motivated and confident to change their behaviour [26]. In the context of school-based obesity interventions, the transtheoretical model can be used to assess where students are in terms of their readiness to change and adjust interventions accordingly. According to this theory, change levels can be set according to arbitrary criteria without considering the social context in which they occur.

The Theory of Planned Behaviour (TPB) assumes that individuals act rationally based on their intentions. The theory states that the most important determinant of a person’s behaviour is their intention to carry out that behaviour [27]. A limitation of TPB is that it does not consider other variables important for behavioural intention and motivation, such as fear, threat, mood or past experiences.

This trial, which is based on the Health Belief Model (HBM), is an approach for assessing an individual’s health behaviour, by examining perceptions and attitudes he/she may have towards diseases, and the negative outcomes of certain actions [20, 21].

### Study setting

Conducted in Arabic schools located in the Klang Valley, this study involves students in grades seven and eight. There are a total of 25 Arabic schools in the Klang Valley, an urban region in Malaysia, with its centre in Kuala Lumpur. Excel software will be used for the random selection and allocation of 4 out of these 25 Arabic schools. The first two schools are assigned intervention groups, while the next two are assigned control groups. Subsequently, 4 classes will be randomly selected from each school. Two of these classes will consist of 13-year-old seventh-grade students, while the next two will consist of mostly 14-year-old eighth-grade students.

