### Sampling method

Simple random sampling will be used for the selection of participants. Two schools will be assigned the intervention group, and two schools the control group, followed by the selection of classes. With this form of probability sampling, researchers use a sampling frame, which includes a list of all students from the selected schools. For this study, a table of random numbers, will be used for the selection of participants, up to the point the sample size is attained. The random selection of participants is achieved by way of Excel software.

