### Data collection

#### Cluster randomized trial flow

*Recruitment of participants*. The teachers and principals will be updated on the study objectives, and the student eligibility criteria, for the cluster randomised controlled trial (RCT). The selection of participants will be conducted at the selected schools. Only those who are available, during the accumulation of data, will be further briefed and assessed on their eligibility, according to the inclusion and exclusion criteria, stated in a screening form. The school administration will forward an invitation, to the parents of eligible participants, to obtain written consent, before the commencement of the study. On receipt of the written consent from students and their parents, the collection of baseline data will begin. The participant information sheet, in English and Arabic, will be made available to eligible students and their parents. The participants will be provided with an explanation, on the objectives and protocols of the study. All participants involved in this study are volunteers, and guaranteed the unrestricted right, to pull out of this study, at any time. Participants will be assured, that all information related to their identities, will be kept confidential. The random selection and allocation of participants, to the intervention or control groups, will be realized through the Excel software. Subsequently, the intervention group will be subjected to the educational intervention. For the post-intervention and follow‐up assessments, the participants will be required to fill in the same questionnaire, albeit, excluding the section referring to personal information.

*Study principles*. This investigation is based on the study protocol item, recommendations for interventional trials (SPIRIT), 2013, statement [23], while complying with the consolidated standards of reporting trials (CONSORTs), statement [30]. The flowchart for the CONSORTs is displayed in Fig 2. CONSORT was developed by a group of researchers not only to identify problems associated with RCTs, but also to present the results of the research in a clear and concise manner, facilitating the reading and assessment of RCTs [30]. The CONSORT 2010 guideline were chosen because it is intended to improve the reporting of parallel- group randomized controlled trials. It enables better understanding of a trial design, conduct, analysis, interpretation and assessment of the validity of its results.

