**Fig 2 pone.0289937.g002:**
[figure not shown]
Consort 2010 flow diagram.

*Randomization*. Randomization is ensured throughout the study, using sealed opaque envelopes. An independent researcher places envelopes enclosing the names of the schools in a box, and randomly selects four envelopes to represent the intervention and control schools. The independent researcher uses Excel software, for the selection of the participants. For this selection process, the IDs of all students will be entered into the datasheet, a random column will be created, and the formula " = RAND()" will be applied. Respondents will be assigned a unique code, for the allocation of a concealment mechanism. This is to circumvent individual-level bias.

*Intervention*. ‘Healthy lifestyle’ intervention is based on the HBM theory, which considers the attitudes and beliefs of adolescents, for the development of their skills and favourable behaviours. A team of health promotion experts, from the University of Malaya’s department of social and preventive medicine, with a special interest in obesity-related behaviour alteration, will assist the researcher, during the designing of the educational health promotion program.

The intervention is specifically designed to:

Provide adolescents with the facts, statistics, and harmful effects, linked to obesity and overweightness.Encourage the consumption of healthy diets, to keep the risks of obesity at bay.Promote the indulgence in physical activity, to reduce the risks of obesity.Inspire students to adopt positive health behaviours.Develop a good decision-making and self-care attitude.Develop the three health belief elements of perceived susceptibility, perceived threat, and perceived benefit vs. barriers.

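### Schools are assigned to arms before students are selected and consented, so recruitment could differ by arm, and two sections speak of allocating participants rather than schools

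*Protocol article*

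**What the plan says.** Three sections assign whole schools, and do so before students are chosen:

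- Study setting: four of the 25 Arabic schools are selected and allocated in one step, "The first two schools are assigned intervention groups, while the next two are assigned control groups". The next step is "Subsequently, 4 classes will be randomly selected from each school".
- Sampling method: "Two schools will be assigned the intervention group, and two schools the control group, followed by the selection of classes".
- Randomization (under Data collection): an independent researcher draws sealed envelopes holding school names and "randomly selects four envelopes to represent the intervention and control schools". Selection of students with a random-number column is described after that.

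Two places speak of participants instead:

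- Abstract, Methods and anticipated results: "The participants will be randomly assigned to the intervention and control groups".
- Recruitment of participants (under Data collection): "The random selection and allocation of participants, to the intervention or control groups, will be realized through the Excel software". This comes after the sentence on consent and baseline: "On receipt of the written consent from students and their parents, the collection of baseline data will begin".

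On how families are approached, the recruitment text says: "The school administration will forward an invitation, to the parents of eligible participants, to obtain written consent".

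**The concern.** In a cluster trial, randomising schools protects the comparison only if the students who enter are recruited in the same way in both arms. If a school's arm is settled before its students are identified and their parents asked, anyone who knows the arm can, without intending to, influence who takes part. Enthusiasm for a healthy-lifestyle programme could raise uptake, or attract more motivated families, in intervention schools only.

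The primary outcome is a self-reported score for knowledge, attitude and practice, which may well depend on motivation. With only two schools per arm there is little averaging: if the schools are of equal size, a shift of d in the students of one school moves the arm mean by d/2.

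The wording on participant allocation adds a second difficulty. A reader cannot tell from the text alone which unit is randomised, or whether this happens before or after consent and baseline.

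**Working it through.** The point is procedural, so the check sets the sections side by side.

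**1. Unit and order by section**

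| Section | Unit assigned | Order relative to students |
|---|---|---|
| Study setting | school | arm fixed at the draw, classes chosen next |
| Sampling method | school | arm first, then classes |
| Randomization | school | schools drawn, then students selected (by sequence of the text) |
| Abstract | participant | none given |
| Recruitment of participants | participant | mentioned after consent and baseline |

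The tool for drawing schools also differs: Excel under Study setting, envelopes under Randomization.

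**2. Where consent falls.** Briefing, eligibility screening, invitation and consent happen inside the selected schools. Under Study setting and Sampling method, selected schools already have an arm. Consent and baseline therefore follow assignment. No section says that they are completed before the allocation is revealed.

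**3. Which steps could differ by arm**

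- Choice of classes: random, so protected.
- Listing of students: random and done by an independent researcher, so protected.
- Availability: only students present at data collection are briefed and screened. Not protected.
- Invitation: sent by the school administration. Not protected.
- Parental consent: a voluntary decision. Not protected.
- Replacement: Sampling method continues selection until the target number is reached. Students who do not enter might therefore be replaced within a school, although the text does not say so.

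**4. What masking covers.** The Intervention section keeps adolescents unaware of the control group. It does not mention parents, teachers, principals or whoever obtains consent, and it describes the trial as single-blind.

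**5. What the analysis covers.** Baseline is one of the GEE time points, and socio-demographic confounders are listed. A difference in baseline score is therefore measured and can be allowed for. A difference in responsiveness to the programme, or in any unmeasured trait, is not.

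**6. Size.** The document gives no uptake rates and no link between willingness to take part and outcome, so no size follows from it. A yardstick for scale can be built, with assumptions. Inputs are the ICC of 0.05 from Sample size, 250/4 = 62.5 students per school, and two schools per arm:

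SE of the arm difference = sqrt(0.05 + 0.95/62.5) = sqrt(0.0652) = 0.255 SD.

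If recruitment shifted a whole arm by an assumed 0.1, 0.2 or 0.3 SD, that would be 0.39, 0.78 or 1.18 standard errors. The shifts are assumptions. The ICC was used for the proportion overweight, not for the questionnaire score. These figures show scale only and are not an estimate of bias.

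**The case against.** The strongest reply is that the design is sound in intent and the article already contains safeguards. Much of this stands.

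- **The unit.** A reader might infer that the unit of randomisation is genuinely in doubt, or that both arms could share a school. The documents do not support that. The trial is labelled cluster-randomised, the sample size uses a design effect, the GEE adjusts for clustering, and three sections assign schools. The participant wording is most likely loose.
- **The reversed order.** The recruitment sentence has no time marker of its own and joins selection with allocation. Selection cannot follow consent and baseline, so the sentence cannot be strictly chronological. It conflicts with the other sections but does not set out a deliberate opposite order.
- **Recruiters knowing the arm.** A reader might infer this as fact. The article says that researchers know the details of the intervention. It does not say that those who recruit know each school's arm, nor that they do not.
- **The envelopes.** It is tempting to say that they conceal nothing once draw order decides the arm. That goes too far. A blind draw by an independent person stops anyone steering a school into an arm, and arm by order of a random draw is valid randomisation. The draw-order rule also stands under Study setting, not in the envelope text. The risk lies in what happens after the draw.
- **Mitigation.** Independent random selection of students and the masking of adolescents do lower the risk. One information sheet is described, with no arm-specific versions. The masking is weaker than it looks, however. Adolescents are meant not to know that they will be re-evaluated, yet under Ethical approval and informed consent they and their parents are told of three rounds of data collection.

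What remains is that availability, school invitations and parental consent come after the arm is fixed, and no stated safeguard covers them.

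**Conclusion.** The point holds as a possible, partly mitigated and unquantified recruitment bias, together with a conflict of wording that must be reconciled. It rests on reading Study setting and Sampling method as written (arm first, then classes and students) and on the absence of any statement that recruiters, school staff or parents are unaware of the arm. It does not show that bias will occur.

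Nor would it be right to say that analysis can do nothing: measured baseline differences can be adjusted for, and only what is unmeasured stays. The size of the bias cannot be estimated from the document. The case for acting is that prevention is cheap, while with two schools per arm and a self-reported primary outcome later correction is only partial.

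**What to change.** 1. Name the school as the only unit of randomisation. Delete the wording in the Abstract and in Recruitment of participants that allocates participants to arms.
2. State one order in every section: draw four schools; select classes and students, obtain consent with one arm-neutral information sheet, and complete baseline in all four; only then have the independent researcher randomise two of the four to intervention.
3. Describe one mechanism for the draw and the allocation, since Study setting and Randomization now name different ones.
4. If recruitment has already begun, report the order actually used and state the recruitment-bias risk as a limitation. The article reports approval from the directors of the selected schools as already obtained, so the schools may already have been drawn.

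The cost is rewording, a re-ordering of steps already planned, and a short wait between baseline and the first session while all four schools finish. No sample-size figure changes.
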